# Remote ischemic conditioning for safety, feasibility and preliminary efficacy of patients with aneurysmal subarachnoid hemorrhage after aneurysm clipping, design, and protocol for an open-label, evaluator blinding randomized controlled trial

**DOI:** 10.3389/fneur.2025.1650773

**Published:** 2025-11-20

**Keywords:** remote ischemic conditioning, aneurysmal subarachnoid hemorrhage, stroke, protocol, brain

## Abstract

**Background and rationale:**

Aneurysmal subarachnoid hemorrhage (aSAH) is a severe cerebrovascular event with a high mortality and disability rate. Compared to interventional surgery, microsurgical clipping is more invasive and has a higher incidence of postoperative complications, including cerebral vasospasm and ischemic cerebral infarction. In recent years, a large number of basic experiments have proved that remote ischemic conditioning (RIC) has multiple pathways of neuroprotective effects, and many large-scale randomized controlled clinical trials have confirmed that remote ischemic conditioning applied to patients with ischemic stroke has the effect of improving prognosis. However, current research has only focused on demonstrating the safety of remote ischemic conditioning for patients with aSAH, and lacks high-level evidence for its effectiveness.

**Method:**

We design an open-label, evaluator blinding randomized controlled trial. This study focuses on aneurysmal subarachnoid hemorrhage occurring within 24 h after microsurgical clipping. All participants will be randomly assigned to the intervention group and the control group at a 1:1 ratio (*n* = 20), and will receive standard management according to the guidelines. Participants assigned to the intervention group will receive RIC twice a day, once in the morning and once in the afternoon, for 7 consecutive days after the operation. Neurological prognosis will be evaluated at baseline, day 3, day 7, day 30, and day 90. The primary outcome measure is the proportion of patients with a mRS score of 0–2 at 90 ± 7 days after surgery and the incidence rate of RIC adverse events. The secondary measures include the incidence of aSAH complications, the mRS score of patients 30 ± 7 days after surgery, and the mRS score of patients 7 ± 1 day after surgery.

**Discussion:**

The study’s aim is to explore the safety, feasibility and preliminary efficacy of RIC in aSAH patients after clipping surgery. It serves as a methodological and feasibility foundation for the later multicenter, double-blind REPAIR trial (NCT06711302), which aims to confirm efficacy in a larger population.

**Clinical trial registration:**

https://clinicaltrials.gov/study/NCT06819657?term=NCT06819657&rank=1, NCT06819657.

## Introduction and rationale

Subarachnoid hemorrhage (SAH) is a severe neurological disorder, with an overall incidence of approximately 9 cases per 100,000 people per year (1, 2). About 85% of non-traumatic subarachnoid hemorrhages are caused by aneurysm rupture (3, 4). Aneurysmal subarachnoid hemorrhage may also be accompanied by neurological complications such as cerebral vasospasm, hydrocephalus, delayed cerebral ischemia, and re-bleeding of the aneurysm (5–7), with a relatively high mortality and disability rate (8). Currently, there are two main treatment methods for aneurysmal subarachnoid hemorrhage worldwide: craniotomy microsurgical clipping and endovascular interventional therapy. According to a meta-analysis, microsurgical clipping has more advantages in closing the aneurysm and reducing the risk of re-bleeding, but it may increase the risk of adverse outcomes and vasospasm (9). In recent decades, although many treatment strategies, such as electrolyte management, and intracranial pressure management, have been studied and widely applied in postoperative management, aSAH patients still have difficulty achieving a good prognosis (10). Therefore, there is an urgent need for new aSAH treatment strategies and methods in clinical practice.

Remote ischemic conditioning (RIC) is a non-invasive treatment for distant organs or tissues (such as the limbs) that involves brief, repetitive ischemia and reperfusion (11). It is a safe and well-tolerated treatment for cardiovascular and cerebrovascular diseases. Numerous large randomized controlled clinical trials have shown that RIC can improve the prognosis of ischemic stroke patients and prevent ischemic stroke in patients with intracranial atherosclerotic stenosis (12–14). Additionally, some basic experiments have demonstrated that RIC can regulate the differential gene expression and inflammatory response processes in mice with subarachnoid hemorrhage, and reduce the incidence of cerebral vascular spasm and improve cognitive dysfunction in experimental mice (15, 16). In patients with aneurysmal subarachnoid hemorrhage, RIC has been proven to be safe and feasible, with the potential to prevent delayed cerebral vasospasm and reduce the incidence of stroke and mortality (17–19). Although previous studies have explored the feasibility or early clinical impact of remote ischemic conditioning (RIC) in aneurysmal subarachnoid hemorrhage (aSAH), high-quality randomized controlled evidence confirming both safety and efficacy after surgical clipping remains limited (17, 20, 21). Therefore, we designed a double-center, open-label, evaluator-blinded pilot randomized controlled trial (NCT06819657) to apply remote ischemic conditioning to aSAH patients who have undergone microsurgical clipping, aiming to explore the safety, feasibility, and preliminary efficacy of unilateral lower limb remote ischemic conditioning in aSAH patients, providing good guidance and reference for the later multicenter, double-blind REPAIR trial (NCT06945239).

## Methods

### Study design

We conduct an open-label, evaluator blinding, randomized controlled clinical trial in People’s Hospital of Ningxia Hui Autonomous Region and Beijing Tiantan Hospital on patients with aSAH who have undergone microsurgical clipping. Subjects who meet the inclusion criteria and do not meet the exclusion criteria will be randomly assigned to the RIC group and the control group within 24 h after microsurgical clipping, as shown in Figure 1. Both groups of subjects will undergo standardized and standardized management. The subjects in the RIC group will undergo remote ischemic preconditioning for 7 consecutive days after enrollment, once in the morning and once in the afternoon each day. The National Institutes of Health Stroke Scale (NIHSS) score will be blindly evaluated by trained researchers at the baseline. The Modified Rankin Scale (mRS) will be blindly evaluated by trained researchers on the 7th, 30th, and 90th days after enrollment.

**Figure 1 fig1:**
[figure not shown]
Trial design flowchart. RIC, remote ischemic conditioning.

All the participants will be enrolled after being fully informed of the content of this clinical study and signing the informed consent form. This study has been approved by the ethics committees of each research center and has been registered on Clinicaltrials.gov, with the registration number being NCT06819657.

### Inclusion and exclusion criteria

Participants will be recruited from the wards. The inclusion criteria are: 1. Imaging examination confirmed aneurysmal subarachnoid hemorrhage. 2. Responsible aneurysms received craniotomy clipping within 24 h. 3. 18 ≤ age ≤80 years old.4. Informed consent of the participant or legally authorized representative. The exclusion criteria are: 1. Patients with other types of cerebral hemorrhage. 2. Prior neurological impairment (mRS Score >1) or mental illness may confuse neurological or functional assessment. 3. Severe comorbidities with a life expectancy of less than 90 days.4. Refractory hypertension (systolic blood pressure 180 > mmHg or diastolic blood pressure 110 > mmHg). 5. RIC contraindications: severe soft tissue injury of lower limbs, peripheral arterial disease or coagulopathy. 6. Simultaneously participate in another research program to study a different experimental therapy. 7. Any condition that the investigator believes may increase the patient’s risk.

### Randomization

In this study, a computer-generated randomization sequence is used to allocate 40 participants to the RIC group and the control group (20 participants in each group) in a 1:1 ratio. Subsequently, the research assistant, who is not involved in the study, seals the group information in sequentially numbered opaque sealed envelopes according to the randomization sequence. All the random envelopes are uniformly stored in a confidential document cabinet before the start of the trial. After completing the participant enrollment screening and the collection of baseline data, the treating physician opens the random envelopes corresponding to the serial numbers and carries out the grouping operation according to the information contained therein.

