#### Secondary outcome measures

The incidence of aSAH complications.The mRS score of patients 7 ± 1 day after surgery.The mRS score of patients 30 ± 7 days after surgery.

This study adopts a blinded assessment design to ensure the objectivity of the data. The data collection and processing flow is as follows: All clinical data at baseline and during the follow-up period are collected by the attending physician and his team. The subjects are assigned a unique code (001-040) according to the order of enrollment. The core outcome indicators are verified by two research coordinators who are not involved in the management of the subjects and remained blinded to the group information, using a double-blind back-to-back assessment model to review the original data. If there are differences during the assessment, they will first be resolved through reviewing the original records and standardized judgment guidelines; if there are still differences, they would be submitted to a third independent assessor for arbitration. Finally, the result data and grouping information will be collected by a researcher and subjected to statistical analysis.

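### One 20:20 list of 40 serves two hospitals and the primary test ignores centre, so arms are balanced only over the whole trial; stratify by hospital.

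*Protocol article*

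**What the plan says.** The introduction of the protocol article states that "we designed a double-center, open-label, evaluator-blinded pilot randomized controlled trial", and Study design names the hospitals as those of "Ningxia Hui Autonomous Region and Beijing Tiantan Hospital". Patients are to be randomized within 24 hours after clipping.

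The Randomization section says that "a computer-generated randomization sequence is used to allocate 40 participants to the RIC group and the control group". The ratio is 1:1, which gives 20 per arm. Assignments go into sequentially numbered opaque envelopes. On custody it says: "All the random envelopes are uniformly stored in a confidential document cabinet"; that sentence is limited to the time before the trial starts. After screening and baseline data collection, "the treating physician opens the random envelopes corresponding to the serial numbers".

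Under Secondary outcome measures, participants are "assigned a unique code (001-040) according to the order of enrollment". The series carries no hospital element.

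Statistical analysis compares groups on categorical variables with Fisher's exact test and states no centre term. The limitations paragraph of the Discussion accepts that baseline imbalance may occur with so few patients, but does not mention imbalance of arm by centre.

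**The concern.** Taken together, these statements describe one list, one overall 20:20 balance and one running enrolment order, shared by two hospitals. Nothing in the method as described keeps the arms balanced within a hospital, and the stated primary test does not allow for centre afterwards. If the hospitals differ in case mix, surgery or intensive care, and so in 90-day mRS, a chance imbalance of arm by hospital passes straight into the unadjusted risk difference. With 40 patients such imbalances are common.

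The practical side is also unresolved. If envelopes are opened in one serial order that matches one enrolment order, the article does not make clear how a treating physician at the second hospital obtains the next one within the 24-hour window. An improvised answer could put envelope order and concealment at risk in an open-label trial. The article presents this pilot as a methodological foundation for a multicentre trial, so multi-site allocation is worth settling here.

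**Working it through.** **Inputs from the article:** 40 patients, 20 per arm, one sequence, two hospitals, unadjusted Fisher test.

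**Assumptions (the article gives no figures):** enrolment split between hospitals from 30/10 to 20/20; gap in good-outcome rate between hospitals of 20 to 40 points, centred on 55%; no treatment effect; envelopes used in sequence, or divided between hospitals without regard to content.

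**1. Chance of imbalance.** With n patients at one hospital, its number X in the RIC arm is hypergeometric (40 slots, 20 RIC, n drawn). The arm difference there is D = 2X − n.

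- n = 20: P(X=10) = C(20,10)²/C(40,20) = 0.248, and P(X=9 or 11) = 0.409. So P(|D| ≥ 4) = 1 − 0.657 = 0.343. Removing P(X=8 or 12) = 0.230 gives P(|D| ≥ 6) = 0.113.
- n = 10 (30/10 split): P(X=5) = 0.284 and P(X=4 or 6) = 0.443. So P(|D| ≥ 4) = 0.273. Removing P(X=3 or 7) = 0.209 gives P(|D| ≥ 6) = 0.065.

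**2. Effect of a given imbalance.** The shift in the risk difference is (D/20) × centre gap.

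- D = 4 (12:8 at equal enrolment): 4/20 × 20, 30, 40 points = 4, 6, 8 points.
- D = 6 (13:7): 6/20 × 20, 30, 40 points = 6, 9, 12 points.

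**3. Average cost in precision, equal enrolment.** With arms balanced within hospitals, the variance of the risk difference is (2/20) × the mean of p(1 − p) over hospitals. The single list adds (gap/20)² × Var(D), where Var(D) = 4 × 20 × 0.25 × 20/39 = 10.26.

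| Gap (rates) | Balanced within hospital | Added by single list | SD, single list | SD, stratified | SD reduction |
|---|---|---|---|---|---|
| 20 points (0.45, 0.65) | 0.0238 | 0.0010 | 0.157 | 0.154 | 2% |
| 30 points (0.40, 0.70) | 0.0225 | 0.0023 | 0.157 | 0.150 | 5% |
| 40 points (0.35, 0.75) | 0.0208 | 0.0041 | 0.158 | 0.144 | 9% |

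At 30/10 the added term is smaller, because Var(D) falls to 4 × 10 × 0.25 × 30/39 = 7.69.

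**4. Type I error.** The exact rejection rate of the two-sided Fisher test at 0.05, averaged over the single list, is 0.024 with equal risks of 0.4 at both hospitals. It is 0.021 to 0.025 with assumed hospital risks of 0.5 v 0.3 or 0.6 v 0.3, at 30/10 and 20/20 enrolment. It stays well below 0.05.

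**5. Predictability.** In a balanced list of length 2k, someone who sees past allocations and guesses the arm with more slots left is right k + (4^k/C(2k,k) − 1)/2 times on average:

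- one list of 40: 23.5/40 = 59%
- 20 slots (10:10) per hospital: 12.3/20 = 62%
- blocks of 10: 6.5/10 = 65%

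**The case against.** A reader might infer that arm and centre are confounded. The article does not support this. Under a random list, arm is independent of centre in expectation, there is no systematic bias, and step 4 shows no inflation of type I error. What remains is chance imbalance, which the limitations paragraph already admits in general terms.

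A reader might also infer that the envelope procedure cannot run at two hospitals. That is not shown either. The cabinet sentence covers custody only before the trial starts, so envelopes could be divided or requested by telephone afterwards. The article does not say which, and either needs squaring with one enrolment-order series and with the treating physician opening the envelope.

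A further objection is that an article condenses a fuller protocol, so silence on stratification proves nothing. That is fair, and the point does not rest on silence. The single sequence, its overall 20:20 balance and the single number series are positive statements. If the full protocol does stratify, the published description needs correcting.

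Finally, the centre gap is assumed. The article describes standardized care, the same device at both sites and a fairly uniform population, so the gap may be below 20 points and the gain below 2%. This stands, and it keeps the point modest.

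**Conclusion.** The point holds as a design improvement of moderate weight. The described method balances arms only over the whole trial, and the stated primary test does nothing about centre. A within-hospital arm difference of 4 or more is a 27% to 34% event for enrolment between 30/10 and 20/20. Its effect on the risk difference is 4/20 of whatever gap exists between the hospitals, and the average precision loss at equal enrolment is about 2% to 9% in SD for gaps of 20 to 40 points. The probabilities depend only on the assumed enrolment split. The shift and the SD figures also depend on the assumed gap, for which the article gives no evidence. The trial's validity is not in question.

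**What to change.** For slots not yet used, generate one concealed 1:1 list per hospital in large or varied blocks. A 20-slot 10:10 list per hospital fits only if enrolment is expected to be equal; otherwise use, for example, blocks of 10. Give each hospital its own numbered envelope set and add a site prefix to the participant code. State in the Randomization section where envelopes are held during enrolment and how each hospital draws the next one.

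Whether or not the list is changed, analyse the primary mRS outcome stratified by centre, for example with an exact stratified test and a Mantel-Haenszel risk difference. Keep the unstratified Fisher test as a sensitivity analysis. Fix this before outcome data are compared by arm.

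The cost is a new list and a second envelope set, with no extra patients. Allocation becomes slightly easier to guess (59% to between 62% and 65%), which matters somewhat because the trial is open-label and the treating physician opens the envelopes. The total may miss 20:20 by a few patients if last blocks are incomplete. A change during recruitment cannot undo imbalance among patients already enrolled, which is a further reason to stratify the analysis.

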**Figure 2 fig2:**
[figure not shown]
The equipment used by the research. **(A)** Patent number: ZL2014108343052; device model: IPC-906H; Beijing Renqiao Cardiocerebrovascular Disease Prevention and Treatment Research Jiangsu Co., Ltd. **(B)** Remote ischemic condition performed in human.

### Outcome

#### Safety outcomes assessment

The safety evaluation indicators are: (1) Mortality rate within 90 days. (2) Adverse events related to RIC (including limb skin injury, local pain, and deep vein thrombosis).

#### Primary outcome measure

The primary outcome measures were the proportion of patients achieving a good functional outcome (mRS score 0–2) at 90 ± 7 days after surgery, and the incidence rate of RIC-related adverse events. The primary endpoint was assessed by blinded neurologists who were not involved in treatment allocation, using standardized interviews.

#### Secondary outcome measures

The incidence of aSAH complications.The mRS score of patients 7 ± 1 day after surgery.The mRS score of patients 30 ± 7 days after surgery.

This study adopts a blinded assessment design to ensure the objectivity of the data. The data collection and processing flow is as follows: All clinical data at baseline and during the follow-up period are collected by the attending physician and his team. The subjects are assigned a unique code (001-040) according to the order of enrollment. The core outcome indicators are verified by two research coordinators who are not involved in the management of the subjects and remained blinded to the group information, using a double-blind back-to-back assessment model to review the original data. If there are differences during the assessment, they will first be resolved through reviewing the original records and standardized judgment guidelines; if there are still differences, they would be submitted to a third independent assessor for arbitration. Finally, the result data and grouping information will be collected by a researcher and subjected to statistical analysis.

### Data monitoring

An independent Data Safety Monitoring Board (DSMB) consisting of one neurosurgeon, one neurologist, and one statistician not involved in the study will oversee data integrity and participant safety. The DSMB will review recruitment rates, adverse events, protocol adherence, and data completeness every three months through both remote and on-site monitoring. All serious adverse events will be reported within 24 h to the DSMB and ethics committees.

### Sample size estimation

Previous studies have shown that a sample size of 10-20 cases per group in a randomized controlled clinical trial is sufficient to fully meet the requirements (22) for feasibility assessment (including core parameters such as recruitment efficiency and intervention compliance). This range is in line with the efficacy calculation standards for pilot studies, and can effectively balance the requirements of scientific research ethics and resource optimization allocation. Assuming a 60% reduction in poor outcomes (mRS>2) in the RIC group compared with controls at 90 ± 7 days after surgery, the sample size calculation indicated that 18 patients per group were required. Thus, 20 patients per group (*n* = 20) were planned for enrollment (α = 0.05, power = 0.80). The calculated minimum sample size was 18 participants per group. Therefore, our goal is to recruit 20 patients per group. The results of this study should be able to determine the initial safety, feasibility, and effectiveness of RIC in aSAH patients, providing good guidance and reference for further conducting large-scale randomized double-blind clinical studies (REPAIR).

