### Statistical analysis

The main analysis adopts the intention-to-treat set, and all randomized subjects are included in the original allocation group; the per-protocol set analysis (PP) is used as a sensitivity analysis supplement. Categorical variables are presented as frequencies and percentages. Group differences will be assessed using Fisher’s exact test because of the small sample size. Continuous variables are subjected to Shapiro–Wilk normality test, and normal distribution data are analyzed using independent sample t-test (mean ± standard deviation), while non-normal data are analyzed using Mann–Whitney U test (median [IQR]). Missing data will be handled using multiple imputation with five imputations. In addition, worst-case and best-case scenario analyses will be conducted as sensitivity checks to assess the robustness of the results. For clinical events such as death, the intention-to-treat principle (ITT) are adopted, and cases of loss to follow-up are classified as no-event outcomes. Statistical analysis will be conducted using the Windows version 26.0 of SPSS statistical software (located in Ammonk, New York, produced by IBM Corporation).

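### The article says the results should be able to determine the initial safety of RIC, which is more than 20 patients per arm and the stated analysis can support

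*Protocol article*

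**What the plan says.** All of this is in the protocol article.

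- **Claim.** Under Sample size estimation: "The results of this study should be able to determine the initial safety, feasibility, and effectiveness of RIC in aSAH patients". The same sentence says this will guide the later REPAIR trial. The Discussion paragraph of the abstract and the end of the Introduction use the weaker verb *explore* for safety, and the Introduction calls the trial a pilot.
- **Safety outcomes.** Safety outcomes assessment lists: "1) Mortality rate within 90 days. (2) Adverse events related to RIC", the latter including skin injury, local pain and deep vein thrombosis. The incidence of RIC-related adverse events is also one of the two primary outcomes.
- **Analysis.** Under Statistical analysis: "Categorical variables are presented as frequencies and percentages", and then "Group differences will be assessed using Fisher’s exact test because of the small sample size". Both are general rules for categorical variables. The article does not say whether the test is one- or two-sided.
- **Size.** Randomization will "allocate 40 participants to the RIC group and the control group (20 participants in each group) in a 1:1 ratio". The stated basis is a rule of thumb for feasibility studies and an efficacy assumption: "Assuming a 60% reduction in poor outcomes (mRS>2) in the RIC group compared with controls at 90 ± 7 days after surgery". No event rate, excess harm or precision target is given for a safety outcome.

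**The concern.** To determine safety, even initial safety, a trial must be able to rule out some amount of harm. The article names no such amount. Its number of patients comes from feasibility and efficacy considerations, and its stated between-group method tests for a difference. With 20 per arm, a non-significant result is likely even when the true excess of deaths or moderately frequent limb events is clinically important.

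The results are meant to inform a larger trial. If the report says that initial safety has been determined, readers will not learn how large a harm remains compatible with the data.

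**Working it through.** **The plan's own figure.** "The calculated minimum sample size was 18 participants per group" refers to mRS>2, not to safety, and the control rate behind it is not given. The usual two-proportion formula is

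n = [1.96·√(2p̄(1−p̄)) + 0.8416·√(p₁(1−p₁) + p₂(1−p₂))]² / (p₁−p₂)²

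with p₂ = 0.4·p₁. For p₁ = 0.76 and p₂ = 0.304 (p̄ = 0.532) it gives (1.383 + 0.528)² / 0.456² = 17.6, so 18. The figure is therefore reached (two-sided, no continuity correction) if the control poor-outcome rate is about 76–77%. It carries no information about power or precision for safety.

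**Inputs for the safety check.** From the article: 20 per arm, Fisher's exact test, α = 0.05. Assumed: a two-sided test, complete follow-up, and the event rates shown below, since the article gives none.

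**1. Which tables reach p<0.05.** With equal arms the two-sided p-value is twice the one-tail probability.
- 4 vs 0: 2·C(20,4)/C(40,4) = 2·4,845/91,390 = 0.106
- 5 vs 0: 2·C(20,5)/C(40,5) = 2·15,504/658,008 = 0.047
- 6 vs 1: 2·[C(20,7) + 20·C(20,6)]/C(40,7) = 2·852,720/18,643,560 = 0.091
- By the same method, 7 vs 1 gives 0.044, 8 vs 2 gives 0.065 and 9 vs 2 gives 0.031.

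So 4 vs 0, 6 vs 1 and 8 vs 2 are all non-significant.

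**2. A doubling of 90-day mortality.** Power is the sum, over all 21×21 tables with p≤0.05, of Bin(a; 20, 2p)·Bin(b; 20, p), where p is control mortality. The chance of missing the doubling is 1 minus that sum.

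| Assumed control | RIC | Missed |
|---|---|---|
| 5% | 10% | 98.3% |
| 10% | 20% | 92.7% |
| 15% | 30% | 87.6% |
| 20% | 40% | 80.8% |
| 25% | 50% | 73.1% |
| 30% | 60% | 65.3% |

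**3. RIC-related events, assuming none in control.** Significance needs at least 5 of 20 in the RIC arm, so the chance of a miss is P(X≤4) for X ~ Bin(20, π).
- π = 15%: 0.0388 + 0.1368 + 0.2293 + 0.2428 + 0.1821 = 83%
- π = 20%: 0.0115 + 0.0576 + 0.1369 + 0.2054 + 0.2182 = 63%
- π = 25%: 0.0032 + 0.0211 + 0.0669 + 0.1339 + 0.1897 = 41%

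The chance passes one half at about π = 23%.

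**4. What 20 exposed patients can exclude.** With 0 of 20 events the exact two-sided 95% upper limit is 1 − 0.025^(1/20) = 16.8%. With 1 of 20 the exact (Clopper–Pearson) upper limit is 24.9%.

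**The case against.** The strongest reply is that this is a declared pilot. The sentence says initial safety, and nowhere does the article claim to detect or exclude a doubling of mortality. Low power for uncommon harms is common to nearly all pilots. Exact intervals and rules of interpretation may well sit in a full protocol or analysis plan that is not shown. This stands in part: the absence of intervals from a condensed article is not the point here. The point is the stated claim, which the article's size and test do not deliver. *Initial* does not repair *determine* while no excluded level of harm is attached to it.

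Three stronger readings should be set aside.

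- A reader might infer that a significance test is the only safety analysis. It is not: frequencies and percentages are also stated, and the primary safety outcome is defined as an incidence rate.
- A reader might infer that a non-significant p-value will be taken as proof of safety. No section says so. Where the Discussion judges an earlier pilot safe, it points to the absence of events.
- A reader might infer that limb harm would probably be missed whatever its rate. With no control events, that is true only below a true rate of roughly 23%. At 30% the test would detect it about 76% of the time.

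The monitoring board's three-monthly review of adverse events and the 24-hour reporting of serious events also protect participants during the trial. They do not provide a basis for the conclusion at its end.

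**Conclusion.** The point holds as a mismatch between a stated conclusion and what the design can deliver. It is not a finding that the trial is unsafe or cannot describe safety.

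The results that need no assumed event rate are that 4 vs 0 and 6 vs 1 are non-significant on a two-sided test, and that zero events in 20 leave rates up to 16.8% compatible with the data. The miss probabilities for a doubling of mortality rest on an assumed control rate and a two-sided test. No single figure, such as the 93% at 10% control mortality, is a property of the plan. The range is about 98% to 65% for control rates of 5% to 30%, so power is 35% or less throughout. A one-sided test would not change the conclusion: at 10% vs 20% the miss probability is still 89%. The figures for RIC-related events assume none in the control arm.

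**What to change.** - **Sample size estimation.** For safety, replace *determine* with *describe* or *explore*, in line with the abstract and introduction. Add what 20 exposed patients can exclude: with zero events, rates above about 17% (exact two-sided 95% limit).
- **Statistical analysis.** Make the safety result the per-arm rate with an exact 95% confidence interval, for 90-day mortality and for RIC-related adverse events. Add the risk difference with a 95% confidence interval for mortality. State that a non-significant Fisher p-value is not evidence of safety. If a full protocol or analysis plan already provides these intervals, refer to it and align the claim with it.

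**Cost.** Two short text changes, with no new data, patients or design change. The downside is a safety statement that looks less favourable.
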